### Ethics

The researchers have obtained approval from the director for health and social affairs in the municipality and from the Regional Committee for Medical and Health Research Ethics (2015/1030/REK sørøst). The trial will be carried out in accordance with the Helsinki Declaration [46]. The participants will be informed both orally and in writing, and written consent to participate will be collected before enrolment by the first author.

People suffering from chronic pain can be vulnerable. It will be important to assure the participants that the study will not inflict harm or include invasive interventions. Nevertheless, there is a possibility that reactions from earlier experiences can occur. The participants will, therefore, receive information on who to contact at the HLC if they need to talk to someone about their reactions.

Adverse events occurring in the sessions will be reported and registered by the instructors. Minor adverse events, e.g. participants being tearful or distressed during the activity [32], will be registered and acted upon after the group-based activity. If more serious adverse events occur, e.g. extreme distress or expressed suicidal thoughts [32], they will immediately be reported to the HLC management and followed up.

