### Interventions

#### Self-management course

The content of the self-management course includes theoretical education, group discussions based on the theoretical input, sharing of experiences and movement exercises. The staff developed the course based on recommendations found in the literature (e.g. [39–41]) and added elements from cognitive behavioural therapy focusing on the participants’ thoughts, emotions and actions. The theoretical part of the course comprises pain theory, barriers in everyday life due to chronic pain, problem-solving, goal-setting and techniques to deal with fatigue, poor sleep, frustrations and isolation. The movement exercises in each session aim to improve balance, posture and breathing, providing the participants with techniques to increase body awareness and the ability to relax. These techniques are essential in Norwegian psychomotor physiotherapy [42] on which this element of the course is built.

Guidelines for how to carry out the course have been developed to help the instructors, ensuring all groups are offered the same content and material (see Additional file 1).

The course is delivered as 2.5-hour weekly group workshops during the daytime for a period of 6 weeks, reaching a total of 15 hours, with 8–10 participants in each group. Two employees who have been dedicated to facilitating the course have a professional background as physiotherapists. All workshops start with the theoretical elements followed by the part of the course introducing movement exercises in a training room. Between the parts, there will be breaks for social interaction. Between each workshop, the participants will be given homework, e.g. working on their goal-setting plan.

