#### Control group

Participants in the control group will be offered a drop-in outdoor easy physical activity, comprising walking and simple strength exercises. The activity will be adjusted to the participants’ physical ability, to keep it both easily accessible and rewarding. The rationale for choosing this activity is that the HLC already offers this activity as a drop-in service without registration or further commitment from people. Offering an activity to all participants in the trial is recognised as ethical and it is good clinical practice [43, 44]. Participation in the control group activity is voluntary, in line with the drop-in policy at the HLC.

The easy physical activity will be delivered as a weekly 1-hour session for a period of 6 weeks. The activity will be in groups with a group size similar to the intervention (8–10 participants in each group) and led by two instructors with skills in physical activity. The group will meet outdoors on a trail popular for walking among the municipality’s inhabitants. However, due to changing weather conditions and according to conditions on the trail, the location might be changed to another area during winter.

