### Documentation of the delivery of the intervention

To document the delivery of the interventions, the instructors will complete an evaluation form for each group. They will be asked to report their experiences with the delivery, the group dynamics and whether there were any adverse events. The instructors will also report the number of participants attending each session.

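### The only adverse-event registration the article describes covers events in the sessions, so it depends on attendance and raw counts by arm would not be comparable

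*Protocol article*

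**What the plan says.** The Ethics section of the protocol article states the rule: "Adverse events occurring in the sessions will be reported and registered by the instructors". Its example of a minor event is tied to the same setting: "Minor adverse events, e.g. participants being tearful or distressed during the activity [32], will be registered and acted upon after the group-based activity". More serious events are passed at once to the management of the Healthy Life Centre (HLC).

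The section on documentation of delivery gives a matching route. For each group, "the instructors will complete an evaluation form for each group", and on content: "They will be asked to report their experiences with the delivery, the group dynamics and whether there were any adverse events". The instructors also count attendance at each session.

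For reactions outside the sessions, Ethics says that participants will "receive information on who to contact at the HLC if they need to talk to someone about their reactions". It does not say whether such a contact is registered as an adverse event.

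Contact time differs by arm. The course consists of "2.5-hour weekly group workshops during the daytime for a period of 6 weeks, reaching a total of 15 hours". For the control arm: "The easy physical activity will be delivered as a weekly 1-hour session for a period of 6 weeks", and "Participation in the control group activity is voluntary, in line with the drop-in policy at the HLC".

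Data collection, Blinding and Secondary outcomes name what is gathered at 3, 6 and 12 months in both arms: the patient-reported scales, the chair-stand test, changes in marital and employment status, and health-care and medication use. No adverse-event item is named among them.

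**The concern.** Both the setting (the session) and the reporter (the instructor) are fixed in the text, so this is a stated rule and not merely a silence. Three features make it a weak rule for this trial.

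- **Unequal opportunity.** The arms differ in session hours by design, and control attendance is optional. A control participant who never drops in cannot have an event registered.
- **Events outside the session.** The course sets homework between workshops, and both arms involve physical exercise. A flare the next day, or distress that surfaces later, falls outside the described route. The Ethics section itself anticipates reactions linked to past experiences.
- **Reporter.** Instructors know the arm because they deliver it. The blinded research assistant is not described as collecting adverse events.

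At stake is what the trial can later say about safety. Raw counts by arm would tend to make the course look worse because more hours are watched. Events that arise outside sessions would be absent from both arms and make both look safer. Someone who stops attending because of an event leaves the one route by which it would be registered.

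**Working it through.** **Inputs.** Six weekly course sessions of 2.5 h (Self-management course). Six weekly control sessions of 1 h with voluntary attendance (Control group). Planned total of 120 participants (Sample size). Per-protocol threshold of three sessions (Statistical analysis). Follow-up to 12 months (Data collection).

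**1. The plan's own figure.** Course hours = sessions × length = 6 × 2.5 = 15 h. The article states 15 h, so the figure is reproduced.

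**2. Control arm.** No total is stated. 6 × 1 = 6 h, an upper bound because attendance is voluntary.

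**3. Maximum time under registration per participant.** Ratio 15 / 6 = 2.5; difference 15 − 6 = 9 h.

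**4. Range with lower attendance.** The article gives no expected attendance. As an assumption, I take three sessions, the per-protocol minimum, as a low value.

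| Course sessions | Control sessions | Hours, course / control | Ratio |
|---|---|---|---|
| 6 | 6 | 15 / 6 | 2.5 |
| 3 | 3 | 7.5 / 3 | 2.5 |
| 6 | 3 | 15 / 3 | 5 |
| 3 | 6 | 7.5 / 6 | 1.25 |

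The course arm is watched longer in every row. With no control attendance the control time is 0 h and no event can be registered.

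**5. What this does to raw counts.** With 120 / 2 = 60 per arm (equal allocation assumed) and full attendance, there are 60 × 15 = 900 person-hours against 60 × 6 = 360. If the event rate per session hour were the same in both arms, the expected counts would still stand at 900 / 360 = 2.5 to 1.

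**6. Calendar time.** The sessions span 6 weeks. Taking 12 months as 52 weeks and the sessions as falling inside follow-up, 6 / 52 = 11.5 % of follow-up falls in the session period. The other 52 − 6 = 46 weeks have no described registration in either arm.

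**7. What the other data cover.**

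| Source | Both arms, regardless of attendance | Records a discrete event | Records relation to activity or stopping |
|---|---|---|---|
| Instructor registration in sessions | No | Yes | Not described |
| Pain, HADS, EQ-5D-5L at 3, 6, 12 months | Yes | No | No |
| Health-care and medication use | Yes | No, use only | No |
| Interviews at 3 and 12 months | Sample of up to 30 | Possibly, in narrative | Possibly, in narrative |

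**8. Primary analysis.** The mixed model uses the patient activation score, not event counts. The estimate and the 55 per arm do not depend on this point.

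**The case against.** The case on the other side is substantial.

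- **The word only is an inference.** The article says what is registered in sessions; it does not exclude other routes. A journal article condenses a fuller protocol, which may contain one. This stands as a limit. The point concerns the route that is described, and here both setting and reporter are stated.
- **Worsening is not lost.** A reader might infer that harm is observed only during session hours, or that people who deteriorate and drop out are missed altogether. The article does not support that. Questionnaires are mailed to both arms whatever the attendance, non-responders are chased, and the analysis follows intention to treat. Deterioration in pain, mood or quality of life can be seen there. The table in the working shows what those data still cannot tell.
- **No harms comparison is planned.** A reader might infer that a planned analysis is biased. None of the objectives, outcomes or analyses compares adverse events between arms, and registering session distress so that it can be acted on is a coherent purpose. This stands and limits the weight of the point.
- **Part of the 2.5 ratio is real exposure.** A longer course gives more opportunity for session-related harm, and someone who never attends cannot be harmed by a session. Since attendance is counted and session lengths are known, a rate per attended person-hour can be worked out. This also stands: the ratio measures opportunity for registration, not the size of a bias.
- **The form per group** does not show that participants are not identified when an event is registered. Correct; the article simply does not describe the link.
- **A questionnaire item is open self-report.** If it asked only about harm linked to the activity, a control who never attended would have nothing to report. That is a fair criticism of such wording, and the item must therefore ask about events regardless of attribution.

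**Conclusion.** The concern holds in a limited form. The adverse-event registration described in the article is tied to sessions and made by unblinded instructors, so it depends on attendance: at most 15 h against at most 6 voluntary hours, a ratio of 2.5 at full attendance and 1.25 to 5 across the attendance scenarios shown. No registration is described between sessions or for about 46 of the 52 weeks. Raw session counts by arm would not be comparable and should not be read as evidence on relative safety.

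This is a cheap improvement to the plan, not a contradiction in it. The conclusion assumes that no further route exists in a fuller protocol; if one does, the point reduces to describing it.

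**What to change.** 1. Add a short item to the 3-, 6- and 12-month questionnaires in both arms: any adverse event or worsening since the last contact, regardless of cause. Follow it with a question on whether the participant relates it to the activity offered and whether it led to stopping. Both arms then have the same observation window.
2. Keep the answers out of sight of the blinded assistant, since participants bring the completed forms to the visit and the text could reveal the arm.
3. Record session events by participant ID. The per-protocol analysis already needs attendance by participant, so the extra work is small. State whether contacts made to the HLC outside sessions are logged.
4. Report adverse events by arm among all randomised participants. Give session events separately, per attended person-hour.

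**Cost.** A slightly longer form and a small amendment; no change in sample size. Enrolment began in August 2015 and was still open when the article was written, so participants already past a follow-up point would have incomplete data, which the report should state. The item remains unblinded self-report, and recall spans up to six months between the last two questionnaires.

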### Methodology for the RCT

#### Data collection

Data will be collected through self-report questionnaires at baseline (*t*_0_), and after 3 (*t*_1_), 6 (*t*_2_) and 12 months (*t*_3_). At baseline, the first author will be available for questions when the participants fill in the questionnaire. The first author will also supervise the physical ability test at baseline. Background variables such as age, gender, marital status, employment status, pain duration, referring institution, other diseases coded with the International Classification of Primary Care 2 (ICPC-2) [47], current medication and health-care utilisation will also be collected at baseline. At the three follow-up points (3, 6 and 12 months), the participants will be sent the questionnaires by mail. The participants will bring the completed self-administrated questionnaires to the follow-up visits, where a research assistant will supervise the physical ability test. There will be one postal reminder for each follow-up data collection point, and non-responders will be contacted by phone or email allowing a delay of up to 4 weeks.

#### Blinding

After allocation, blinding is not possible due to the intervention’s nature. However, a research assistant blinded to allocation will conduct the physical ability test at *t*_1_, *t*_2_ and *t*_3_. The research assistant will have a protocol describing how to perform the physical ability test and which data to collect (changes in marital status, employment status, and current use of health care and medication), and the participants will be asked not to divulge their allocation.

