However, reaching and engaging those likely to benefit from participation in self-management interventions have been described as insufficient, leading to high attrition rates and low uptake [11, 12]. Difficulties in accessing health services and health-care personnel are described by patients as barriers to participation in different types of self-management interventions [13–15]. As self-care support is acknowledged as a key in management of LTCs, a sustainable number of resources has been invested in offering these interventions [6, 16]. Delivering easily accessible self-management interventions, therefore, seems to be significant in providing a sustainable health service, and primary care and community health-care services seem to be the suitable arenas for them [12].

In a Norwegian context, group-based patient education as a self-management activity has traditionally been offered in hospitals (see general introduction in [17]). Recent health reforms promote support for self-care to be carried out also in the local communities [18]. This action aims to offer interventions that are easy to access. In addition, the Norwegian Directorate of Health has since 2004 encouraged municipalities to establish Healthy Life Centres (HLCs) as part of their public health care [19]. HLCs are low-threshold health-care services delivering easily accessible activities and interventions in the communities. These services aim to support people at risk with health behavioural changes and in managing chronic conditions [19, 20]. The government writes that the theoretical framework of HLCs’ interventions should be in salutogenesis [20], where strengthening people’s capacities to use their own and available health resources is central [21].

One group utilising HLCs comprises people with long-lasting pain. Long-lasting or chronic pain is a widespread LTC that affects up to one-third of the population [22–24]. The condition affects the physical, social and psychological dimensions in life [25–27]. Pain sufferers often describe problems of sleeplessness, depression, poor quality of life, and exhaustion, as well as interference with physical ability, social relations and work life [23, 28, 29]. An increase in the number of people struggling with chronic pain is documented [22, 23]. It has an impact on society in terms of increased health-care utilisation, sick leave and early retirement [1, 23, 30].

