### Setting

HLCs (“Frisklivssentral” in Norwegian) are a public service offered by municipalities as part of the Norwegian community health-care system [19]. The HLCs strive to offer easily accessible interventions with few barriers for participation. They aim to give a low-threshold health-care service that people can attend with or without referral from others. In addition, a HLC receives referrals from general practitioners, physiotherapists and the Norwegian Labour and Welfare Administration [20].

Our project is situated at a HLC in a city in central Norway serving a population of approximately 185,000 inhabitants. The centre has 5.5 positions occupied by multidisciplinary health professionals with a bachelor’s or master’s degree. The HLC offers several group-based activities and interventions, e.g. indoor and outdoor physical activity, healthy diet courses, smoking cessation programmes and courses focusing on coping with depression or anhedonia. The drop-in physical activity offered to the control group is an example of an activity at the HLC where people can attend without referral or further commitment. In cooperation with patient organisations, the HLC staff developed the self-management course constituting the intervention arm in this trial.

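### The assistant who must stay blind for the chair-stand test also collects current health-care use: an avoidable risk of accidental unblinding

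*Protocol article*

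**What the plan says.** Under Blinding, the article accepts that blinding after allocation is not possible in general, and then makes one exception: "a research assistant blinded to allocation will conduct the physical ability test" at each of the three follow-up points. The next sentence says that this assistant will work from a protocol covering how to run the test and "which data to collect (changes in marital status, employment status, and current use of health care and medication". The same sentence gives a safeguard: "the participants will be asked not to divulge their allocation".

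Under Data collection, the follow-up questionnaires reach participants by another route: "the participants will be sent the questionnaires by mail". Participants then bring them, completed, to the visit at which the assistant runs the test.

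Two other sections bear on what counts as health care. The Background states: "HLCs are low-threshold health-care services delivering easily accessible activities and interventions in the communities". The Setting section adds: "The drop-in physical activity offered to the control group is an example of an activity at the HLC". It also says that the centre's staff developed the course, together with patient organisations.

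**The concern.** One person is given two duties that pull against each other. The assistant must not learn the arm, yet is also told to find out what health care each participant is using. Since the article treats the centre's activities as health care, a participant who answers fully may name the course or the walking group. The participant is then asked to report care use and to withhold one part of it, to the same person at the same visit.

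What is at stake is the only blinded outcome measurement in the trial. Every other listed outcome is reported by participants who know their arm. If the assistant learns the arm before or during the test, the protection against detection bias is lost for that measurement. If the same person tests the participant again, it may be lost for later visits too.

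**Working it through.** The plan gives no figure on this point, and nothing in the article allows a probability of disclosure or a resulting bias to be calculated. The check is therefore a comparison of passages, with simple arithmetic on timing and exposure.

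**1. Is the chair-stand test the only outcome that is not self-reported?** The Primary outcome and Secondary outcomes sections list PAM, the Brief Pain Inventory, a pain VAS, the Pain Self-Efficacy Questionnaire, HADS, EQ-5D-5L, AIOS and SOC-13. These are eight self-report instruments. The ninth measure, the 30-second chair-stand test, is the only one based on performance, and it is secondary.

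**2. Do the two duties fall on the same person?** Yes. Blinding assigns both the test and the additional data to one assistant role at 3, 6 and 12 months.

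**3. Could an answer about health care reveal the arm?** Yes, if the participant names the activity. The Background and Setting sections place both activities within a health-care service. The activities are different, so naming one identifies the arm. Mentioning the centre without the activity does not, because both arms attend it.

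**4. Would the activity still be current at the visits?** The Self-management course section says: "The course is delivered as 2.5-hour weekly group workshops during the daytime for a period of 6 weeks". The Control group section gives the same six-week period.
- Six weeks in months: 6 × 12/52 = 1.4.
- Gap between the end of the activity and the visit = visit month − start lag − 1.4, assuming that visits are counted from baseline.
- The article does not state the start lag, so a range is shown.

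| Start lag (months) | Gap before 3-month visit | 6-month visit | 12-month visit |
|---|---|---|---|
| 0 | 1.6 | 4.6 | 10.6 |
| 1 | 0.6 | 3.6 | 9.6 |
| 1.6 | 0 | 3.0 | 9.0 |

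The course would still be running at the 3-month visit only if it began more than about 1.6 months after baseline (13 − 6 = 7 weeks). Some lag is plausible, because participants are gathered into groups of 8–10. With 60 per arm (120/2, equal arms assumed), that is about 60/10 = 6 to 60/8 = 7.5 groups per arm, filled as recruitment proceeds. The recall period behind the word for current use is not given either. A long one would bring the activity back into scope.

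**5. How often does the occasion arise?** At most 120 participants × 3 visits = 360 assessments before dropout. This counts the occasions on which the item is collected, not disclosures.

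**6. Does it touch the primary analysis?** No. PAM is completed by the participant on a form, and the assistant does not rate it. The sample size is built on PAM and is not involved.

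**The case against.** The strongest reply is that the plan already protects the blind, and that a truthful answer need not break it. The item asks about current use, and an activity that started near baseline would have ended well before every visit. Both arms attend the same centre, so mentioning it gives nothing away. Participants are asked to keep their allocation to themselves and can report visits to a general practitioner or physiotherapist without naming the trial activity. The assistant's own protocol, mentioned but not shown, may fix the order of test and questions or exclude the trial activities. If the questions come after the test, that visit's measurement is safe whatever is said. Participants know their arm in any case, so differences in effort would remain even with a perfectly blind assessor.

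Most of this stands, and it limits the point. A reader might infer that the procedure is likely to unblind the test, or that an honest answer must name the course. The article supports neither reading. It also does not say that the items are asked aloud (though collection at the visit is the natural reading), that the same individual tests at every visit, or that knowing the arm would change the count.

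The reply does not remove the risk. The timing argument depends on a start lag and a recall period that are not given. The Control group section describes the walking activity as a service the centre already runs, so its use after the six weeks is conceivable. The request for silence is harder to keep when the listener is also asking about care. Testing first protects only that visit if the same assistant returns. The assignment of both duties to one person is a stated choice, not a detail left out of a condensed article.

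**Conclusion.** The point holds as a foreseeable and avoidable risk of accidental unblinding, not as a demonstrated likelihood. It affects one secondary outcome at three follow-up visits. That outcome is the only objective one and the only one for which the plan arranges a blinded assessment. PAM is unaffected. The size of any bias cannot be derived from the article.

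This rests on three readings: the assistant obtains these items from the participant at the visit, the health-care item is not worded to exclude trial activities, and the questions are not always kept until after the test. Carry-over from 3 months to later visits further assumes that the same assistant tests again. If the assistant's protocol already settles these matters, the remaining action is to say so. It is a minor weakness in procedure, worth correcting because correction is cheap. The Trial status section reports recruitment still in progress, so visits remain that can be protected.

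**What to change.** Preferred: move the health-care, medication, marital-status and employment items into the questionnaire that is already mailed before each follow-up. Because completed questionnaires are brought to the visit, have them handed over in a sealed envelope that the assessor does not open. The assessor's instructions would then cover the chair-stand test only.

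At minimum: perform the chair-stand test before these questions at every visit, and word the health-care item so that it excludes the two trial activities. This leaves some risk of carry-over if the same assistant tests at later visits.

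In either case, have the assessor record at each visit whether the allocation became known and whether this was before or after the test, so that the integrity of the blind can be reported.

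Cost: a few extra questionnaire items and envelopes, and slightly more missing data on these four items than when the assistant collects them. None of the four is listed as an outcome, so that loss is small.
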